#### Biofeedback training

Participants in this group will undergo an electromyography (EMG) biofeedback training for the trapezius and frontalis using a rose for relaxation 3 times per week for 6 weeks. Each session will be 30 minutes, with a 5-minute resting period between each muscle session. Fig 6 summarizes the biofeedback training protocol.

**Fig 6 pone.0291534.g006:**
[figure not shown]
Protocol of biofeedback training. a- biofeedback training device, b- frontalis electrdode placement, c- training device display/feedback, d- trapezius electrode placement.

Neurotrac myoplus 4 pro instrument will be used for EMG biofeedback training. The rose game for relaxation provides an EMG biofeedback when the participant’s rose opens when relaxation is detected, and the aim is to relax completely and stay relaxed. 4 microvolt is the default value which can still be lowered one’s relaxation ability is achieved. During each training session, the electrodes will be placed on Frontalis and Trapezius muscle. The electrodes are connected to this machine that gives feedback to the participant via a visual signal, allowing them to decrease or increase muscle activity. During the training sessions, the patient will be made to sit in a comfortable chair with a straight back, feet flat on the floor (forming 90 –degrees with knees and with arm-rest and instructed to maintain erect sitting throughout [48].

### Placebo group

The placebo group will receive the patient education sheet with basic information about migraine in terms of symptoms, triggers, and prevention tips.

### Compliance during the experimental study

The participants need to complete 18 sessions within 6 weeks duration (3 times a week or alternative days)

#### Termination criteria

The termination criteria are based on ACSM guidelines for exercise testing/ prescription [49] and migraine trust [50]:

Absolute termination: Onset of moderate to severe angina [51], signs of poor perfusion: pale appearance to the skin, bluish discoloration, excessive cold and clammy skin, severe or unusual shortness of breath (modified Borg’s scale), ataxia (failure of muscle coordination), vertigo (an illusion of dizzying movement), visual or gait problems and confusion Migraine induced headache Relative termination: Any chest pain that is increasing shortness of breath (modified Borg’s scale), leg cramps/ fatigue, patients’ request.

#### Safety consideration

The participants will be encouraged to: Wear comfortable clothing and well-padded shoes that can protect the heels and arches of their feet. Perform warm-up before doing aerobic exercises and cool-down after exercises to reduce the risk of strains and sprains. If there is dizziness, shortness of breath, chest pain, nausea, vomiting, and joint pain during excise, stop the activity. The temperature in the aerobic area is to be maintained at a moderate level, with good ventilation. Schedule regular days off from exercise and rest when tired.

### Statistical methods

#### Analysis of EEG signals

Amplitude and frequency, frequency band ratio, power spectrum density, and coherence will be analysed for resting-state EEG recording. The recorded data from the MUSE 2 portable EEG device can be further analysed in MATLAB. The data obtained will be imported to MATLAB using EEGLAB function plugins (muse monitor app) CSV file. Once imported, the pre-processing steps will be done to run Independent Component Analysis (ICA). The sampling frequency will be set at 256Hz. To remove linear trends, high-pass filtering at 1 Hz will be done to obtain good quality Independent Component Analysis (ICA) decompositions. Average referencing for source localization will be done since a non-scalp reference is used. Artifact rejection and ICA will be used to remove artifacts such as muscle, eye blinks, or eye movements without removing the affected data portions.

After extracting epochs and plotting data, the EEG amplitude, frequency, frequency band ratio, power spectrum density, and coherence will be analysed. EEG will be decomposed into the five EEG sub-bands of frequency and amplitude: delta (0.5–3 Hz/ 5–250 microvolt), theta (4–7 Hz/ 20–100 microvolt), alpha (8–12 Hz/ 5–120 microvolt), beta (13–30 Hz/ 5–50 microvolt) and gamma (31–40 Hz/ -10 microvolt). MATLAB will design a filter with the ’butter’ command for frequency band ratio, setting the cut-off frequencies according to alpha or theta band or appropriate bands and then using it on data with the ’filter’ command.

The power spectral density of EEG will be estimated using AR Burg method. The AR method is based on modeling the data sequence x(n) as the output of a causal and discrete filter whose input is white noise, which is expressed as the follows:

$$x\left(n\right)=-\overset{p}{\underset{k=1}{\sum }}a\left(k\right)\cdot x\left(n-k\right)+\omega \left(n\right)$$

where a(k) is the AR coefficient, x(n) is the white noise of variance equal to r2, ω(n) is window function and p is the order of the AR model.

Next, the coherence estimation will be performed. Coherence represents the normalized covariance of two time series in the frequency domain. Mathematically, the coherence function C_xy_(f) at a frequency f for signal x and y is obtained by the normalization of the cross-spectral spectrum as follows:

$$C_{xy}\left(f\right)=\frac{\left|\langle P_{xy}\left(f\right)\rangle \right|}{\sqrt{P_{xx}\left(f\right)}*\sqrt{P_{yy}\left(f\right)}}$$

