**Result:**

After the primary EEG analysis using MATLAB, the amplitude, frequency, frequency band ratio, and power spectrum density will be analysed. Mixed design analysis and intention-to-treat analysis will be used to assess the efficacy of aerobic training.

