### Study goal and objective

If an earlier, migraine is left untreated or undiagnosed, it is reported that around 2.5% of individuals with migraine are considered to have a chronic condition, defined as presenting with more than 15 headache days within a month. Subclassifications of the disease (migraine with and without aura and chronic migraine) occur clinically at various severity levels and coexist with numerous comorbidities. For this reason, several studies encourage a multidisciplinary and tailored treatment approach for these patients [26,27]. This preliminary randomized control trial aims to analyse the effectiveness of aerobic training among university students with migraine symptoms. The main objective is to determine the preliminary effect of aerobic training on migraine pain level, sleep quality, quality of life, and resting-state brain waves compared with EMG biofeedback training and placebo.

The alternative hypothesis of this study will be the aerobic training will be superior to EMG biofeedback training and placebo group in improving migraine pain level, sleep quality, quality of life, and resting-state brain waves. The null hypothesis will be the aerobic training is same as to EMG biofeedback training and placebo group in improving migraine pain level, sleep quality, quality of life, and resting-state brain waves. Although the Migraine Research Foundation listed three main types of non-drug treatments for migraine: lifestyle advice, therapies, and exercises. Some common aerobic exercises such as walking, jogging, a behavioral weight loss program, cycling, and a combination of cross-training, walking, jogging, and cycling are suggested to be beneficial to migraine patients but there remains no specific protocol established till now. Hence, this study will contribute to the research field by establishing an aerobic training protocol for patients with migraine symptoms.

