### Outcomes

The primary endpoint is resting-state EEG, and the secondary endpoints are sleep quality, quality of life, and migraine pain level. The Confounders will be the level of migraine pain (Russo et al., 2018), gender (Victor et al., 2010) (Kelman, 2006), and age (Echiverri et al., 2018), COVID-19 (Haghdoost et al., 2021).

The migraine pain level questionnaire that records the general health condition of the participants and the characteristics of migraine which including, frequency, severity, and duration will be included. Level of pain scored on a four-point numerical rating scale (0–3) equivalent to no, mild, moderate, and severe pain [36]: 0 no pain. 1 mild pain, does not interfere with usual activities 2 moderate pain, inhibits but does not wholly prevent usual activities 3 severe pain, prevents all activities. The other components are expressed as either decreased/ increased/ remains the same/ unable to recall.

Pittsburgh Sleep Index is a self-rated questionnaire that assesses sleep quality and disturbances over a 1-month interval. 19 individual items generate seven component scores: subjective sleep quality, sleep latency, duration, habitual sleep efficiency, sleep disturbances, use of sleeping medication, and daytime dysfunction. The sum of scores for these seven components yields one global score. The sleep component scores are summed to yield a total score ranging from 0 to 21, with the higher total score (referred to as global score) indicating worse sleep quality [37].

Migraine Specific Quality of life is a 14-item instrument that measures the impact of migraine across three essential aspects of a patient’s health-related quality of life over the past 4 weeks: role function-restrictive (RR), role function-preventive (RP), and emotional function (EF). Raw dimension scores are computed as a sum of item response and rescaled from a 0 to 100 scale. The higher the score better is the quality of life [38].

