Recording of resting-state EEG will be performed using MUSE 2 a portable EEG recording device. The headset has four dry sensors (two mastoid and two forehead sensors). It fits over the ears and extends at an angle over the middle of the forehead when properly fitted with 3 reference electrodes. Once the headband is fitted, as shown in Fig 2b, the mind monitor app will be used for data acquisition. There will be horse to represent the sensors on the Muse and its connection. Solid ovals indicate a good connection, outlines indicate a poor connection and an empty space indicates no connection. The data acquisition space will be 100–200 cm from the computer/ tablet monitor displaying the stimulus presentation sequence. In the mind monitor application, the presentation of brain wave sequence can be in absolute, raw, discrete, accelerometer, and spectrogram views. In this study, raw EEG presentation values will be used for stimulus presentation sequence. So, each sensor’s raw data will be recorded in microvolts (μV). The sensors will be TP9 (left ear), AF7 (left forehead), AF8 (right forehead), TP10 (right ear), AUXR (right auxillay). The participant will be instructed not to clench teeth and blink eyes often since it can alter the activity recorded. The resting-state EEG will be recorded for a total of 20 minutes alternating between eyes open and eyes closed condition [39–41]. Details of the SPIRIT enrollment and the experimental protocol are as illustrated in Figs 1 and 2.

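### The primary endpoint is named only as resting-state EEG: no single variable and no direction of benefit is fixed, although superiority is hypothesised and the trial is sized on one test at 5%.

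*Protocol article*

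**What the plan says.** Under Outcomes the protocol article states: "The primary endpoint is resting-state EEG, and the secondary endpoints are sleep quality, quality of life, and migraine pain level". The opening of Methodology names the same primary endpoint and adds no detail.

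The section Analysis of EEG signals says what will be taken from the recording: "Amplitude and frequency, frequency band ratio, power spectrum density, and coherence will be analysed for resting-state EEG recording". It also says "EEG will be decomposed into the five EEG sub-bands of frequency and amplitude". For the band ratio, the filter is to be designed by "setting the cut-off frequencies according to alpha or theta band or appropriate bands", so the bands that form the ratio are left open. The Result paragraph of the abstract gives a shorter list, "the amplitude, frequency, frequency band ratio, and power spectrum density will be analysed", without coherence.

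Outcomes lists four main sensors (TP9, AF7, AF8, TP10) and an auxiliary one, and says "The resting-state EEG will be recorded for a total of 20 minutes alternating between eyes open and eyes closed condition".

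Study goal and objective gives the alternative hypothesis that "the aerobic training will be superior to EMG biofeedback training and placebo group in improving migraine pain level, sleep quality, quality of life", and the sentence goes on to include resting-state brain waves. Sample size uses one between-groups F test with effect size 0.4, alpha 0.05 and three groups. Statistical analyses names a mixed design analysis and intention to treat.

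**The concern.** A superiority claim needs a variable on which it is judged and a direction that counts as better. For pain, sleep quality and quality of life, the direction follows from the scales described under Outcomes. For the primary endpoint the article gives neither. A reader cannot tell whether higher alpha power, a lower theta ratio or a change in coherence would confirm the hypothesis, or whether the opposite change would refute it.

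The primary result could therefore be chosen after the data are seen, from whichever measure happens to reach significance. The 5% level used for the sample size would then not describe the real chance of a false positive primary finding.

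A second, smaller matter is that the hypothesis concerns aerobic training against each of two comparators, while the sized test is a three-group F test. That test does not say which groups differ.

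**Working it through.** **1. The plan's own figure.** Inputs from Sample size: f = 0.4, alpha 0.05, 0.95 (printed as beta error, read here as power), 3 groups, 4 measurements, N = 66, dropout 25%. The correlation between measurements is not stated; 0.5 is assumed.

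- λ = N·f²·m / [1 + (m − 1)ρ] = 66 × 0.16 × 4 / (1 + 3 × 0.5) = 42.24 / 2.5 = 16.9.
- The noncentral F with 2 and 63 degrees of freedom gives power 0.958, so 66 reproduces.
- 66 / 0.75 = 88, so the final size reproduces too.

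The trial is thus sized for one test of one variable at 5%. (The article has only two assessment times, so the input of 4 measurements is open to question. That is a separate matter and does not affect this point.)

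**2. What the primary endpoint contains.**

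| Element | Number | Section |
|---|---|---|
| Kinds of measure | 5 (4 in the abstract) | Analysis of EEG signals; abstract, Result |
| Frequency bands | 5 | Analysis of EEG signals |
| Main sensors | 4 | Outcomes |
| Eye conditions | 2 | Outcomes |
| Measure named as primary | none | – |
| Direction named as benefit | none | – |

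**3. Error rate if any one measure may count.** Each measure is tested two-sided at 0.05, with no true effect.

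- Independent measures: 1 − 0.95^k. For k = 4 this is 18.6%; for k = 5, 22.6%.
- Five measures with equal pairwise correlation (assumed; the article gives none): 18.3% at 0.5, 12.8% at 0.8, 10.2% at 0.9.
- If the five measures were each tested in five bands (25 tests): 72.3% if independent; 47% at correlation 0.5, 24% at 0.8, 16% at 0.9.

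**4. The two contrasts.** Aerobic against biofeedback and aerobic against placebo share the aerobic arm, so with equal arms their correlation is 0.5. On one variable, each contrast tested two-sided at 0.05:

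- Either contrast may count, with no gate: 9.1%.
- Both must succeed: 0.9% when both nulls are true, and never above 5%.

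Requiring both does not cure step 3. If one contrast is sure to succeed, the other is null, and any of five measures may count, the error is 22.7%, 18.3% or 12.8% at correlations 0, 0.5 or 0.8.

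**5. The F test.** The effect size f depends only on the spread of the three group means, not on which group stands apart. If biofeedback alone differs and aerobic training equals placebo, f = 0.4 gives the same power, 0.958. A significant F test alone therefore does not establish the stated hypothesis.

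**The case against.** **The trial is called a pilot, and a multiplicity rule may stand in an analysis plan that is not shown.** This is fair as far as it goes, and the absence of a multiplicity rule is not the point made here. But which variable is primary is a basic element of the protocol. The article has room for filter commands and for the autoregressive and coherence formulas, and it still names no primary variable. It also states a superiority hypothesis and sizes for 0.95 power, so the pilot label does not settle the matter.

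**A reader might infer that the two contrasts themselves break the 5% level.** The document does not support this. The hypothesis joins the comparators with *and*. If aerobic training must beat both, each contrast can be tested at 0.05 without adjustment, and the price is power. The 9% figure needs a rule under which either contrast suffices without a gate, and the article states no such rule.

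**A reader might infer that well over a hundred EEG variables are primary and each is tested at 0.05, so that a false positive is almost certain.** Crossing measures, bands, sensors or sensor pairs, and eye conditions can give 156 variables: 40 for amplitude, 40 for power spectral density, 60 for coherence, 8 for frequency and 8 for one ratio. But the article does not say that each cell is tested, and 0.05 appears only among the sample-size inputs. A mixed design analysis could carry band, sensor or condition as within-subject factors. Near-certainty also depends on the correlation: 156 tests give about 86% at 0.5, 40% at 0.8 and 24% at 0.9. Amplitude and power in the same band and sensor are closely related, so high correlations are plausible at least there.

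**The F test may be meant for sizing only, with contrasts to follow.** This stands. The article never says that the F test alone will carry the claim. What remains is that it could not do so.

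**Conclusion.** The concern holds in this form: the primary endpoint is not fixed to one variable with a direction of benefit, while superiority is hypothesised and one 5% test is sized. If any of the five kinds of measure may count, the false-positive chance is about 10% to 23%, which is two to more than four times the nominal level. The range rests on assumed correlations from 0.9 down to 0, on one test per kind of measure, and on each test being made at 0.05. Finer testing by band, sensor or eye condition raises it. The list of measures also differs between the abstract and the EEG section, and the ratio bands are open, so the content of the primary endpoint is itself unsettled.

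The contrasts are a matter of stating the success rule. They do not by themselves exceed the 5% level if both are required.

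**What to change.** Before any data are seen, name one primary EEG variable in full: measure, band, sensors, eye condition and the week 6 time point. State which direction of change counts as benefit. Eyes-closed alpha-band power from the AR-Burg spectrum would be one example, but nothing in the article singles it out. The investigators should choose the variable and justify both it and its direction.

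State that superiority will be claimed only if aerobic training against placebo and aerobic training against EMG biofeedback are both significant at two-sided 0.05 on that variable, in the stated direction. With both required, alpha need not be split.

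Label all other EEG measures exploratory. Make the abstract and the EEG section list the same measures, and fix the bands of the ratio.

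The cost is wording only, and controlling the error rate this way needs no extra participants. The other EEG measures lose confirmatory status. Keeping all five kinds as co-equal primaries with a Bonferroni split (alpha 0.01 each) would, on the plan's own inputs and correlation 0.5, raise N from 66 to 87, or 87 / 0.75 = 116 with dropout. At N = 66, power would fall from 95.8% to 85.8%.

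### The EEG is high-passed at 1 Hz before delta is measured as 0.5–3 Hz, so the delta values of the primary endpoint will not describe the band they name

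*Protocol article*

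**What the plan says.** The Outcomes section makes the EEG primary: "The primary endpoint is resting-state EEG, and the secondary endpoints are sleep quality, quality of life, and migraine pain level". No band is singled out there.

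The section on analysis of EEG signals gives the steps in order. After import comes pre-processing: "Once imported, the pre-processing steps will be done to run Independent Component Analysis (ICA". The filter belongs to this stage: "To remove linear trends, high-pass filtering at 1 Hz will be done to obtain good quality Independent Component Analysis (ICA) decompositions". Re-referencing, artifact rejection and ICA follow. The measures come after that: "After extracting epochs and plotting data, the EEG amplitude, frequency, frequency band ratio, power spectrum density, and coherence will be analysed". Next, "EEG will be decomposed into the five EEG sub-bands of frequency and amplitude", with the lowest band given as "delta (0.5–3 Hz/ 5–250 microvolt". The other four bands start at 4 Hz or higher.

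The section does not give the filter type or order, or what the 1 Hz figure marks (half-power point, half-amplitude point or passband edge). It does not mention a second, less filtered copy of the data.

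**The concern.** Two figures in one section do not fit together. A filter meant to suppress activity below 1 Hz comes before a measurement whose band starts at 0.5 Hz. If the plan is followed as written, a value labelled 0.5–3 Hz is partly the roll-off of the filter. It cannot be compared with delta from a study that measured the full band. Activity at 0.5–1 Hz also counts for less in the total than its label implies, so a treatment effect concentrated there would be diluted. Delta is one of the five bands that make up the primary endpoint, and the band-wise measures all inherit the mismatch when they use delta.

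**Working it through.** The plan states no figure for the loss, so there is none to reproduce.

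**Inputs from the protocol article (analysis of EEG signals).** High-pass 1 Hz; delta 0.5–3 Hz; sampling rate 256 Hz ("The sampling frequency will be set at 256Hz").

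**Assumptions, not in the document.** Power spectrum S(f) proportional to 1, 1/f or 1/f². Filter designs: a sharp cut; Butterworth of order 1, 2 or 4 with half-power at 1 Hz; and a Hamming-window FIR filter with about 1 Hz transition width, with 1 Hz read either as the half-amplitude point or as the passband edge.

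**Step 1: share of the bandwidth below the cut-off.** (1 − 0.5)/(3 − 0.5) = 0.5/2.5 = 20%.

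**Step 2: share of unfiltered delta power at 0.5–1 Hz.**
- Flat: 0.5/2.5 = 20%.
- 1/f: ln 2/ln 6 = 0.387, or 39%.
- 1/f²: (2 − 1)/(2 − 1/3) = 0.60, or 60%.

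These are also the losses under a sharp cut at 1 Hz.

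**Step 3: attenuation at 0.5 Hz.** A Butterworth high-pass of order n at 1 Hz passes a power fraction of 1/(1 + (1/f)^(2n)). At f = 0.5 this is 1/5, 1/17 and 1/257 for n = 1, 2 and 4, or about 7.0, 12.3 and 24.1 dB. The FIR filter gives about 59 dB if 1 Hz is its half-amplitude point, and 6.0 dB if 1 Hz is its passband edge.

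**Step 4: share of total delta power lost.** Loss = 1 − ∫S(f)|H(f)|²df / ∫S(f)df over 0.5–3 Hz.

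| Filter | Flat | 1/f | 1/f² |
|---|---|---|---|
| Sharp cut at 1 Hz | 20% | 39% | 60% |
| Butterworth, order 1 | 31% | 42% | 53% |
| Butterworth, order 2 | 24% | 39% | 56% |
| Butterworth, order 4 | 21% | 39% | 59% |
| FIR, half-amplitude at 1 Hz | 25% | 44% | 65% |
| FIR, passband edge at 1 Hz | 6% | 13% | 23% |

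The range is about 6% to 65%. As root-mean-square amplitude the ends are 1 − √(1 − 0.058) = 3% and 1 − √(1 − 0.651) = 41%.

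**Step 5: what remains at 0.5–1 Hz.** For the Butterworth filters and the FIR filter with half-amplitude at 1 Hz, 64–97% of the power there is lost, so 3–36% remains. With the passband edge at 1 Hz, 29–39% is lost and about 62–71% remains.

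**Step 6: loss above 1 Hz.** With a gentle filter the loss does not stop at 1 Hz. For the first-order Butterworth and a flat spectrum, the part below 1 Hz contributes 0.644 × 0.20 = 0.129 of the total loss of 0.314. The remaining 0.185 comes from 1–3 Hz. This matters for where a restated delta band should start.

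The percentages are for power. Coherence is normalised frequency by frequency, so they do not carry over to it as they stand. What carries over is that a delta coherence labelled from 0.5 Hz rests, below 1 Hz, on an attenuated signal.

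**The case against.** The strongest defence is that the article condenses a fuller pipeline. Filtering is tied to preparing for ICA, and the text does not say which copy of the data is epoched. A common practice is to estimate ICA on a 1 Hz copy and carry the weights back to less filtered data; if that is intended, the conflict disappears. This part does not stand. The article gives both numbers and a sequence of steps, and the natural reading is one data stream. The filtering sentence also gives removal of linear trends as a purpose, which is a treatment of the data themselves. For the same reason it would be wrong to say that the 1 Hz cut-off is there for ICA alone.

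The points on size do stand. A reader might infer that 0.5–1 Hz is removed altogether and that an arm difference there could not be seen. That holds only for a steep filter; with the passband edge at 1 Hz, most of the power there survives. A reader might also infer a biased treatment comparison. The documents do not support that: the same linear filter scales each frequency by the same factor in every participant at baseline and at week 6. Nor is the whole primary endpoint compromised. Theta, alpha, beta and gamma are essentially untouched, no hypothesis names delta, and the ratio step mentions alpha and theta by name and leaves other bands open, so a delta ratio is possible but not certain. The trial is also a pilot.

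**Conclusion.** The concern holds in a limited form. The high-pass cut-off and the lower delta limit conflict as written, and nothing in the article reconciles them. Delta power is reduced in every case examined. The size depends on a filter design and a spectrum that the document does not give, so the 6–65% range rests on those assumptions and is not an estimate for this trial. The consequence is a mislabelled, less comparable delta measure with reduced sensitivity to the slowest activity. It should be corrected before the data are analysed, so that the definition of delta is not settled after results have been seen. It changes neither the sample size nor the other four bands.

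**What to change.** State the filter type, order and meaning of the 1 Hz figure, and then choose one of two routes.

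1. Keep the single 1 Hz filter and restate delta's lower limit at or above the filter's passband edge, in the band list, in every measure or ratio that uses delta, and in the report. Where 1 Hz is the passband edge, delta can start at 1 Hz, and the share of its bandwidth below the cut-off falls from 20% to 0%. Where 1 Hz is a half-power or half-amplitude point, the limit has to be somewhat higher. The cost is one changed band limit and a narrower delta. This route fits the stated wish to remove trends.

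2. Estimate the ICA weights on the 1 Hz copy, apply them to a copy high-passed clearly below 0.5 Hz, and measure all bands there. Delta stays at 0.5–3 Hz. The cost is a few lines of MATLAB/EEGLAB code and somewhat more slow drift in delta, which weighs against the trend-removal purpose.

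Neither route affects recruitment, sample size or treatment.

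### The EEG pipeline filters out part of the delta band that it then analyses and, read in sequence, computes coherence on a four-sensor average reference that distorts it

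*Protocol article*

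**What the plan says.** The Outcomes section makes resting-state EEG the primary endpoint and names no single band or measure. It describes the device as follows: "The headset has four dry sensors (two mastoid and two forehead sensors". It then lists five channel names: "The sensors will be TP9 (left ear), AF7 (left forehead), AF8 (right forehead), TP10 (right ear), AUXR (right auxillay".

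The section on analysis of EEG signals gives the processing in this order:

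1. High-pass filter: "high-pass filtering at 1 Hz will be done to obtain good quality Independent Component Analysis (ICA) decompositions".
2. Re-reference: "Average referencing for source localization will be done since a non-scalp reference is used".
3. Artifact rejection and ICA, to remove muscle, blink and eye-movement activity.
4. Epoching, after which "the EEG amplitude, frequency, frequency band ratio, power spectrum density, and coherence will be analysed".

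The lowest band is "delta (0.5–3 Hz/ 5–250 microvolt". The next three are "theta (4–7 Hz/ 20–100 microvolt), alpha (8–12 Hz/ 5–120 microvolt), beta (13–30 Hz/ 5–50 microvolt", and gamma is 31–40 Hz. Coherence is defined as the absolute cross-spectrum divided by the square roots of the two auto-spectra, so its sign is lost.

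**The concern.** Two stated steps work against measures that the same section goes on to analyse.

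**Delta.** The filter cut-off lies inside the delta band. Nothing in the text says that the ICA solution is carried back to data filtered at a lower frequency. What is reported as delta would then not be the band that the article defines.

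**Average reference.** Subtracting the mean of all channels is meant for dense scalp coverage. With four sensors, the subtracted mean contains a quarter of every channel, so each channel is mixed into the others. The stated purpose is source localization, but no source-localization outcome is listed anywhere in the article.

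At stake is the meaning of parts of the primary endpoint. Delta power could be largely a product of the filter. Coherence could move in the opposite direction to true coupling. Forehead activity could show up as a change at the ear sensors.

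**Working it through.** The article gives no figure of its own on this point to reproduce. Its inputs are the 1 Hz high-pass, delta 0.5–3 Hz, four sensors, an average reference, and magnitude coherence. The filter type and order, the spectral slope and the channel covariances are not given, so they are assumed below and shown as ranges.

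**1. Delta band**

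- Share of bandwidth below 1 Hz: (1 − 0.5)/(3 − 0.5) = 0.5/2.5 = 20%.
- Share of delta power between 0.5 and 1 Hz:
  - flat spectrum: 20%
  - 1/f spectrum: ln(1/0.5)/ln(3/0.5) = ln 2/ln 6 = 0.387
  - 1/f² spectrum: (1/0.5 − 1/1)/(1/0.5 − 1/3) = 1/1.667 = 0.60
- These shares equal the loss only for an ideal cut at exactly 1 Hz. For real filters, over slopes from flat to 1/f²:

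| Meaning of 1 Hz | Filters tried | Delta power lost |
|---|---|---|
| Cut-off frequency | Butterworth order 2 or 4, single or forward-backward pass; Hamming FIR with −6 dB at 1 Hz | 21% to 70% |
| Passband edge only | Hamming FIR with −6 dB at 0.5 Hz | 6% to 23% |

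Theta starts at 4 Hz, so the four higher bands lie wholly above the cut-off.

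**2. Average reference over four channels**

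The operation is H = I − J/4, where J is the matrix of ones. A channel covariance (or cross-spectral) matrix S becomes H S Hᵀ. The four re-referenced channels sum to zero at every time point, so the rank falls from 4 to 3.

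- *Independent channels, equal variance.* Variance = 0.75 and covariance = −0.25, so the correlation is −1/3 and the magnitude coherence is 0.33. True coherence is 0. A simulation of four independent white-noise channels, 10 minutes at 256 Hz, gave 0.333 with the average reference and 0.038 without it.
- *Equal variance, common correlation r.* H S Hᵀ = (1 − r)(I − J/4), so r cancels from the correlation. Values of r = 0, 0.2, 0.5 and 0.8 all give −1/3. A change in common coupling is invisible.
- *One coupled pair with correlation r, other pairs 0, equal variance.* Covariance of that pair = 0.625r − 0.25 and variance = 0.75 − 0.375r:

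| True r | After average reference | Magnitude |
|---|---|---|
| 0 | −0.33 | 0.33 |
| 0.2 | −0.19 | 0.19 |
| 0.5 | +0.11 | 0.11 |
| 0.8 | +0.56 | 0.56 |

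The reported magnitude first falls and then rises as the true coupling increases.

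- *Forehead activity reaching the ears.* Assume independent channels with ear variance 1. With forehead variance 4, ear power = 9/16 + (1 + 4 + 4)/16 = 1.125, ear–ear covariance = −0.375 + 8/16 = 0.125, and coherence = 0.11. With forehead variance 1, ear power = 0.75, covariance = −0.25, and coherence = 0.33. Ear power falls by 33% and ear–ear coherence triples, with nothing changed at the ears.

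**3. Channel list**

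Four sensors are described and five are named. If the auxiliary channel entered the average, independent equal-variance channels would show a coherence of 1/(5 − 1) = 0.25 instead of 0.33. The text does not say which applies.

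**The case against.** **ICA may be fitted on the 1 Hz data and its weights transferred.** Then there would be no delta loss, and a full analysis plan might say so. But the article sets out the filter and the band as consecutive steps and mentions no transfer, so the two figures conflict as written. What stands is that the size of the loss cannot be pinned down. Sub-1 Hz activity is attenuated, not necessarily removed.

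**The average reference is tied to source localization, and the reference for coherence is not stated.** This is fair, and it is why confidence is lower here. The order of the steps nevertheless puts the average reference before every measure, and no step restores the recorded reference. Coherence is also missing from the list of EEG measures in the abstract, although the methods section includes it.

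**The −1/3 result is a special case.** Correct. With independent channels and forehead variance nine times ear variance, the mean pairwise correlation is −0.285, with −0.565 for the forehead pair and +0.429 for the ear pair. With both left–right pairs correlated 0, 0.3, 0.6 or 0.8, the mean magnitude is 0.333, 0.333, 0.556 or 0.758. A reader might infer that coherence would carry no information about the signal. That does not follow: it is distorted, not disconnected.

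**The pipeline is the same for all groups and both visits, and the assessor is blinded.** A reader might infer an established between-group bias, since the biofeedback arm trains the frontalis, which lies under the forehead sensors. The mixing shown above is a possible route. Its size depends on how well ICA removes forehead artifact, since a component that ICA removes is removed from every channel. No bias is demonstrated.

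**Conclusion.** The concern holds in two parts, both worth fixing before analysis.

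- **Delta: high confidence.** The 1 Hz filter and the 0.5–3 Hz band contradict each other. The affected share is 20% of the bandwidth and about 6% to 70% of delta power, under assumed filters and slopes from flat to 1/f².
- **Coherence and ear-channel power: moderate confidence.** If the steps are applied in the order given, a four-sensor average reference reduces the rank to 3. It gives unrelated equal-variance channels a coherence of 0.33, hides common changes among equal-variance channels, and makes pair coherence non-monotone in the true coupling.

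A reader might conclude that the whole primary endpoint is invalid. The article does not support that. Four of five bands lie above the filter cut-off, and the coherence problem depends on a reference that the text leaves open. The extra channel name is an inconsistency to reconcile, not a demonstrated error in the analysis.

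**What to change.** 1. Fit ICA on a copy high-passed at 1 Hz and apply the weights to data high-passed at or below 0.5 Hz. Alternatively, redefine delta as 1–3 Hz wherever it appears. State the filter type, order and cut-off definition.
2. Drop the average reference, since no source-localization outcome exists. If it is kept for another purpose, do not compute band power or coherence on those data.
3. Compute band power on the recorded reference from TP9, AF7, AF8 and TP10 only, and reconcile the five-name list with the four-sensor headset.
4. State the reference used for coherence, and label coherence as exploratory.

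The cost is wording and analysis script only, with no extra participants, visits or recordings. The downside is that the recorded reference is itself not neutral: noise shared through it also raises coherence. That is why coherence should stay exploratory after the change. Redefining delta as 1–3 Hz would also make the band narrower than the one now stated.
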